##### Emotional security and physical safety

To assess the severity and intensity of the violence that children have been exposed to, a combined measure will be used including items from the Conflict Tactics Scale (78 items, 8-point rating scale) [64], the Conflict Tactics Scale parent child (27 and 39 items, 8-point rating scale) [64], the Parents Report of Traumatic Impact (21 items ) [65], and the Adverse Childhood Experience Questionnaire (10 items, 5-point rating scale) [66]. An example item is *I punched or hit my partner with something that could hurt*. This combined questionnaire has been used in a previous study on the effectiveness of a psycho-educational prevention program for children exposed to IPV [67]. The questionnaire covers the topics and duration of the violence and the nature of the arguments in the relationship with the (ex-partner), followed by items from the Conflict Tactics Scale parent child and Parents Report of Traumatic Impact about problems between parent and child, and traumatic events the child has experienced. The questionnaire also includes items about traumatic experiences in parents’ own childhood. A short questionnaire of 8 items for parent and child is added to assess if any new IPV incidents or other stressful events occurred.

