##### Parent functioning

To assess parental stress, the Nijmegen Ouderlijke Stress Index—short version (NOSI-K) [84] will be used. The NOSI-K is a short version of the Parenting Stress Index [85] and a 25-item parent-rated questionnaire. The NOSI-K measures the stress related to the parent-child relationship and uses a 6-point scale (1 = totally disagree, 6 = totally agree). An example item is *I often have the feeling I cannot handle things very well*. Cronbach’s alpha for mothers and fathers is .90 and .91, respectively [86], and the NOS-K has moderate concurrent, discriminate, and criterion validity [84, 87].

To measure caregivers’ trauma knowledge, we will use a short self-report questionnaire developed for the training “Caring for Traumatized Children” [88]. The questionnaire comprises 6 items that reflect the six primary training goals, rated at a 10-point scale (1 = not accomplished, 10 = totally accomplished). Higher scores indicate higher trauma knowledge. An example item is *You know what the impact of trauma is on the development and behaviour of your child*.

Trauma symptoms in caregivers will be assessed with the Impact of Events Scale – Revised (IES-R) [89]. The Dutch version “Schokverwerkingslijst (SVL-22)” was developed by [90]. This questionnaire consists of 22 items measuring symptoms of PTSD during the last week. The SVL-22 measures three dimensions: intrusion (9 items), avoidance (8 items), and hyper-arousal (6 items). Parents rate the items on a 5-point Likert scale ranging from “not at all” (0) to “extremely” (4). An example item is *Any reminder brought back feelings about it*. Internal consistency was high (alpha = .88) [91]. Support construct validity is found in a Dutch study [90].

The Young Adult Self-Report [92] will be used to assess the psychopathology symptoms in parents. The short version of 29 items will be used in this study with items rated on a 3-point scale (0 = not true, 2 = often true). An example item is *I am too dependent on others*. The Dutch version has good reliability and validity [93]. In a Dutch study, Cronbach’s alpha was 0.92 [23].

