## Statistical methods

### Statistical methods for primary and secondary outcomes {20a}

The measurement level of each variable is at least ordinal. We control for the duration and severity of family violence [96], child functioning, parental psychopathology [97], and new incidents of family violence as a priori potential confounders. Analyses will be performed using the latest version of the software package Statistical Package for the Social Sciences (SPSS). First, to determine whether changes on continuous measures are different per treatment, we use linear mixed models. Continuous measures with only one time point will be analysed with independent samples *T*-test. Changes in categorical outcomes over the course of treatment across the conditions are tested with generalized estimating equations (GEE). To handle missing data, we will use maximum likelihood estimation within the linear mixed model analyses. For the planned GEE, we will explore the possibilities to deal with missing data, depending on the amount, randomness, and type of data missing. Analyses will primarily be performed according to the principles of intention-to-treat; however, they will be repeated as per-protocol analyses (see Table 4).

**Table 4 Tab4:** Statistical analyses

*Statistical analyses*					
	Measure	Type of data	Timepoints	Statistical analysis	Subjects
Child PTSD	CAPS-CA	Categorical	3	GEE	ITT/PP
	CRIES	Continuous	4	Mixed models	ITT/PP
	TSCC	Continuous	3	Mixed models	ITT/PP
Child functioning	SDQ	Continuous	3	Mixed models	ITT/PP
	CDI	Continuous	3	Mixed models	ITT/PP
	CDC	Continuous	3	Mixed models	ITT/PP
Parent functioning	NOSI-K	Continuous	4	Mixed models	ITT/PP
	Trauma-informed	Continuous	3	Mixed models	ITT/PP
	TSI	Continuous	3	Mixed models	ITT/PP
	YAS-R	Continuous	3	Mixed models	ITT/PP
	DPAS	Continuous	3	Mixed models	ITT/PP
Structural emotional and physical safety	CTS	Continuous	3	Mixed models	ITT/PP
	CTS-pc	Continuous	3	Mixed models	ITT/PP
	PRTI	Continuous	3	Mixed models	ITT/PP
	ACE-Q	Continuous	3	Mixed models	ITT/PP
	New IPV incidents	Continuous	4	Mixed models	ITT/PP
	SIS	Continuous	3	Mixed models	ITT/PP
	SIFS	Continuous	3	Mixed models	ITT/PP
	SIM-PR	Continuous	3	Mixed models	ITT/PP
	Security scales	Continuous	3	Mixed models	ITT/PP
	FIT	Categorical	1	Independent samples T-test	ITT/PP

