Descriptive and exploratory analyses will be carried out by standard methods. All continuous scores will be examined for normality. If variable distributions deviate too much from normality, corrective steps will be taken either by transforming variables or by using non-parametric tests. We will control for child functioning, parental psychopathology, duration, severity, and intensity of interparental violence, and new IPV incidents. The variables are treated as covariables in the analyses mentioned below.

To examine our primary hypothesis, linear mixed models will be used in case of continuous data. GEE will be used for the categorical data. We will use the end of treatment (T12/T14) and intermediate/follow-up time-point (T13) to compare FITT with ITT (objective 1).

To examine our secondary hypotheses, linear mixed models will be used. We will use the end of treatment time-point (T12/T14) to compare FITT with TAU. Control measures are child functioning; parental psychopathology; duration, severity, and intensity of interparental violence; and new IPV incidents. The variables are treated as covariables in the up-mentioned analyses. We will use the Benjamini-Hochberg method to correct for multiple comparisons.

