### Methods in analysis to handle protocol non-adherence and any statistical methods to handle missing data {20c}

If children and families drop out from treatment, we will try to continue measurements according to the randomized treatment condition and analyses will primarily be performed according to the principles of intention-to-treat. This means families are analyzed as participants of the treatment condition they are randomized to. However, analyses will be repeated as per-protocol analyses, which means that families are analysed as participants of the condition they actually received.

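### Maximum likelihood in the adjusted mixed models does not cover missing parent-reported covariates, so a child with complete self-report can lose outcome rows from an analysis called intention-to-treat

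*Protocol article*

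**What the plan says.** All references are to the protocol article. ITT below means the intensive trauma treatment arm; intention-to-treat is written out.

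- **Missing data, section {20a}.** For the mixed models: "To handle missing data, we will use maximum likelihood estimation within the linear mixed model analyses". For the categorical outcomes the method is left open: "For the planned GEE, we will explore the possibilities to deal with missing data, depending on the amount, randomness, and type of data missing".
- **Covariates, section {20a}.** "We will control for child functioning, parental psychopathology, duration, severity, and intensity of interparental violence, and new IPV incidents". Their role is fixed too: "The variables are treated as covariables in the analyses mentioned below". The text does not say whether they are T0 values or values at each visit.
- **Sources of the covariates.** The Parent functioning section says the Young Adult Self-Report "will be used to assess the psychopathology symptoms in parents", and Table 3 lists it (YAS-R) with the parent as sole respondent. Table 3 also gives the CTS as parent-only. New incidents have both informants: "A short questionnaire of 8 items for parent and child is added to assess if any new IPV incidents or other stressful events occurred". They are measured at T0, during treatment, at end of treatment and at follow-up.
- **Analysis set.** Section {20a}: "Analyses will primarily be performed according to the principles of intention-to-treat; however, they will be repeated as per-protocol analyses". Section {20c} explains that under intention-to-treat "families are analyzed as participants of the treatment condition they are randomized to".

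**The concern.** Likelihood estimation in a mixed model is a sound answer to missing outcomes. It is no answer to missing covariates. The model is written conditional on the covariates, so a row without one contributes nothing to the likelihood. The article puts covariates that only a parent can supply into models for outcomes that the child reports, and then names a method that does not cover them.

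The set actually analysed would then lean towards children whose parents returned the forms. At the least, that loses information on primary outcomes that were in fact observed. If return of parent forms also depended on arm and on prognosis, the randomised FITT versus ITT comparison would lose some of its protection against selection.

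**Working it through.** **1. Which models are exposed.** Table 4 assigns mixed models to CRIES, TSCC, SIS and SIFS. All have child report, all sit under the primary outcomes, and all fall under the covariate rule. CAPS-CA is assigned to GEE, where missing-data handling is explicitly open. The FIT is assigned to a t-test, which carries no covariates. The problem is confined to the adjusted linear mixed models.

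**2. Which covariates depend on the parent form.** YAS-R and CTS have no child version. The child-reported CTS-pc covers problems between parent and child, so it is no evident substitute for interparental violence. SDQ and new incidents have child versions and the CDI is child-report, so child functioning and new incidents need not be empty when the parent form is missing.

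**3. Child or visit.** Take 40 children per arm, three visits, 20% of outcomes missing at the last visit (2.8 expected outcome rows per child), and assumed missing parent forms of 10% in FITT and 20% in ITT.

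- T0 covariate: 40 × 0.10 + 40 × 0.20 = 12 children expected lost, and 12 × 2.8 ≈ 34 outcome rows. A simulation of 300 runs gave 12.3 children (4.1 FITT, 8.2 ITT) and 34 rows.
- Per-visit covariate at the same rates: 0.7 children and 34 rows.

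The row loss is the same; only its pattern differs. Per-visit use is awkward for CRIES in any case. Table 3 collects CRIES at T1–11 but not YAS-R or CTS, so that reading would delete every T1–11 CRIES row.

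**4. The plan's own sample size.** Section {14} uses f = 0.18, correlation 0.5, ε = 1, two groups, two measurements and two-sided 5%. For the within-between interaction, λ = f² × N × m / (1 − ρ), with 1 and N − 2 degrees of freedom. At N = 64, λ = 0.0324 × 64 × 2 / 0.5 = 8.29 and power is 0.809. The stated 64 reproduces as the smallest even N reaching 80%. Three arms of 32 make 96, and 96 / 0.8 = 120, the stated target. Two arms therefore randomise 80.

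**5. Power with missing parent forms.** The article gives no rate, so a range is shown, taking whole children as lost (the T0 reading). Base 64 treats the loss as additional to the 20% allowance. Base 80 assumes every randomised child otherwise contributes.

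| Assumed missing | From 64: N, power | From 80: N, power |
|---|---|---|
| 0% | 64, 0.809 | 80, 0.889 |
| 10% | 57.6, 0.766 | 72, 0.854 |
| 20% | 51.2, 0.714 | 64, 0.809 |
| 30% | 44.8, 0.654 | 56, 0.754 |

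**6. Could loss differ by arm?** Section {16b} has measurement start after the allocation has been given to the centre, so even T0 forms may be completed with the arm known. Tables 1 and 2 give FITT parents sessions and ITT parents none. With assumed loss of 5% in FITT and 20% in ITT from 32 per arm, 30.4 and 25.6 children remain. The equal-arm equivalent is 4 × 30.4 × 25.6 / (30.4 + 25.6) = 55.6, with power 0.750.

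**The case against.** **This is detail for the analysis plan.** An article may leave the handling of missing covariates to a document not shown, and its sentence on maximum likelihood is correct for outcomes. That limits the point but does not remove it. The article prescribes the covariates, names the method and claims intention-to-treat. Carried out as written in SPSS mixed models, the three do not fit together. For GEE it leaves the matter open; for the mixed models it presents maximum likelihood as the answer.

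**A reader might infer that a missing parent form removes the child from every model.** The documents do not support that. GEE handling is open, the FIT t-test has no covariates, several covariates have a child version, and a covariate used per visit costs only that visit.

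**A reader might also infer that ITT will lose more children.** This is conceivable, but no completion rate is given for either arm. Under {10}, caregivers in all arms must be able to take part, and Table 3 sets the same parent battery for everyone.

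**A reader might expect a definite bias.** A simulation with 5% loss in FITT, 25% in ITT and loss more likely where the child improved less (logit slope 0.7 per SD) gave a bias of −0.12 SD of change, power 0.59 and type I error 7.2%. All three inputs are invented. The scenario also ties loss of whole children, which needs a missing T0 form, to improvement that happens later, so it needs an unstated common cause. It illustrates a mechanism and does not estimate this trial's bias.

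**The 20% allowance may absorb some of the loss.** This stands: families without parent forms may overlap with dropouts, which is why both bases are shown.

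**Conclusion.** The point holds for the adjusted linear mixed models, including those for child-reported primary outcomes. The stated method does not cover missing YAS-R or CTS values, so observed child outcomes would be discarded: all of a child's rows under T0 covariates, or single visits under per-visit covariates. That contradicts the intention-to-treat statement in {20a} and {20c}.

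The magnitude rests on an assumed rate. At 20% missing forms, power lies between 0.71 and 0.81, depending on how far the loss overlaps with the existing allowance; at the upper end, missing forms alone use up that allowance. Differential loss between FITT and ITT is possible. Its direction and any resulting bias are unknown. The change is worth making because the loss is avoidable at almost no cost.

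**What to change.** Amend {20a} and {20c} to say that:

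- covariates are T0 values only, so that new incidents of violence after randomisation are not adjusted for;
- no outcome row is dropped because a covariate is missing;
- missing T0 covariates are imputed from T0 data without using arm, or by multiple imputation;
- the number of imputed values is reported per arm.

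Arm-blind imputation protects the comparison only if T0 values are themselves untouched by allocation, and {16b} leaves that in doubt. So either complete the T0 battery before allocation is disclosed, where feasible, or add a sensitivity mixed model adjusted only for the baseline value of the outcome.

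The cost is a few sentences and a little more analysis work. Moving the T0 battery ahead of disclosure also needs a change in the order of procedures at the centres; the sensitivity model does not.

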#### Sample size {14}

Power analysis was conducted to determine whether an informative trial could be conducted given limitations imposed upon the maximum sample due to the duration of the study and size of the population of children indicated for trauma treatment, using G*power 3 [95]. Sample size calculation was made based on the assumptions of the primary objective and the first secondary objective. A priori, we decided that adding systemic intervention elements to individual trauma therapy would be justified if it would mean that on average at least one out of five children would have clinically significant benefit when given the full FITT compared to treatment without systemic elements (number needed to treat = 5; equivalent to *f* = 0.18).

For primary objective 1 (Does intensive trauma therapy with a family-based component (FITT) lead to a stronger reduction of trauma symptoms and stronger increase of structural emotional safety than intensive trauma therapy without this family-based component (ITT)?), the sample size was calculated based on between 2 groups by within effect with at least two measurements (pre, end/follow-up), setting *f* = 0.18 with a power of 80% and a significance level of 5% (two-sided). Default settings were used for the correlation among repeated measures (= 0.5) and non-sphericity correction (*ε* = 1). According to the power analysis, a total sample size of 64 children is required.

Secondary objective 1 (Does intensive trauma therapy with a family-based component (FITT) lead to faster reduction of trauma symptoms and increase of structural emotional safety than low-frequency trauma treatment with parent therapy and family sessions?) is based on two measurements (pre and intermediate/follow-up). In accordance with the first sample size calculation, we tested with setting *f* = 0.18 with a power of 80%, a significance level of 5% (two-sided) was used. Again, default settings were used for correlation among repeated measures (= 0.5) and non-sphericity correction (*ε* = 1). Based on this calculation, a total sample size of 64 children is required.

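### The non-normality rule looks at raw scores rather than model residuals, and one of its two remedies, non-parametric tests, would drop the covariates, repeated measures and likelihood handling of missing data planned for the mixed model

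*Protocol article*

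**What the plan says.** All the relevant text is in the protocol article, section Statistical methods for primary and secondary outcomes {20a}.

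- Main model: "First, to determine whether changes on continuous measures are different per treatment, we use linear mixed models". Table 4 assigns mixed models to 19 of its 21 measures; the exceptions are the CAPS-CA (GEE) and the FIT (t-test).
- Missing data: "To handle missing data, we will use maximum likelihood estimation within the linear mixed model analyses".
- Analysis set: "Analyses will primarily be performed according to the principles of intention-to-treat; however, they will be repeated as per-protocol analyses".
- Distribution check: "All continuous scores will be examined for normality".
- Remedy: "If variable distributions deviate too much from normality, corrective steps will be taken either by transforming variables or by using non-parametric tests".
- Covariates (child functioning, parental psychopathology, features of the interparental violence, new incidents): "The variables are treated as covariables in the analyses mentioned below".

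The section does not say how a non-parametric test would retain the covariates, the repeated measurements or the incomplete cases.

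**The concern.** **The trigger is aimed at the wrong quantity.** A linear mixed model does not need normally distributed scores. It assumes normal residuals and random effects. Raw scores in this trial can be skewed for reasons the model copes with: Eligibility criteria {10} requires at least intrusions and avoidance, which cuts off the lower end at baseline, and successful treatment pushes later scores towards the floor. The rule can therefore fire when the planned model is adequate.

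**One permitted remedy conflicts with the neighbouring commitments.** The usual two-group rank tests take no covariates, compare one time point or one change score, and use only participants with that value observed. Where that branch is taken, the question moves from a covariate-adjusted difference in change, valid under missing-at-random, to a comparison of distributions among completers. Sample size {14} allows 20% for loss to follow-up and measurement unreliability together, so incomplete cases are expected.

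**Reach.** The check covers all continuous scores. These include the CRIES, TSCC and emotional security scales listed as primary, and the violence and incident scores, which are the likeliest to be skewed. Some outcomes could end up tested by mixed models and others by rank tests, under different hypotheses.

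**Working it through.** **1. Reproduce the plan's own figure.** Sample size {14} gives f = 0.18, two groups, two measurements, correlation 0.5, two-sided 5%, power 80%, and a total of 64. For the within-between interaction, the noncentrality is λ = f²·N·m/(1 − ρ) = 0.18² × 64 × 2 / 0.5 = 8.29, with 1 and 62 degrees of freedom. Power is 0.797 at N = 62 and 0.809 at N = 64, so 64 reproduces. With 32 per arm and SD 1, the SD of change is √(2(1 − 0.5)) = 1. Setting δ² × 64/4 = 8.29 gives δ = 0.72 SD, the design effect.

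**2. Power at the design effect, 32 per arm, ρ = 0.5 (normal approximation).**
- Baseline-adjusted model: residual SD = √(1 − 0.5²) = 0.866, so 0.72/0.866 × √(32/2) = 3.33 and power = Φ(3.33 − 1.96) ≈ 0.914.
- Rank test on post scores, relative efficiency 0.955: 0.72 × √(32 × 0.955/2) = 2.81 and power ≈ 0.804.

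Simulation (2,500 runs per setting):

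| Setting, δ = 0.72 | Baseline-adjusted | t on change | Rank, post | Rank, change |
|---|---|---|---|---|
| 32 per arm, normal | 0.906 | 0.813 | 0.791 | 0.794 |
| 32 per arm, skewed baseline, normal residuals | 0.897 | 0.798 | 0.802 | 0.790 |
| 40 per arm, 20% random loss, normal | 0.905 | 0.807 | 0.776 | 0.785 |
| 32 per arm, log-normal, shift effect | 0.871 | 0.776 | 0.985 | 0.958 |

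The second row is the misfiring case: scores are skewed, the model is adequate, and the rank test costs about 10 points against baseline adjustment. The last row runs the other way.

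**3. Power with dropout related to severity.** Assumptions not in the article: 40 per arm, true difference 0.62 SD, normal data, dropout logit −1.4 + 0.7 × baseline in both arms (about 20% lost).

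| ρ | Baseline-adjusted | Rank, post | t on change | Rank, change |
|---|---|---|---|---|
| 0.5 | 78% | 66% | 69% | 66% |
| 0.6 | 84% | 65% | 78% | 75% |
| 0.7 | 92% | 65% | 88% | 86% |

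At the article's correlation of 0.5 the loss is 78 − 66 = 12 points against baseline adjustment and 69 − 66 = 3 against a change analysis. Change against change, it is 3, 3 and 2 points across the three correlations.

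With log-normal data and the same dropout:
- Baseline-adjusted against rank on post scores: 66% v 65%, 74% v 66% and 80% v 65%.
- t on change against rank on change: 49% v 55%, 54% v 63% and 66% v 73%, a gain for the rank test.

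**4. Type I error, no true difference, normal data, 40 per arm, same dropout slope of 0.7.**
- Same direction in both arms: about 5% for either method.
- Severity-dependent in one arm only: about 5 to 6.5% for the rank test.
- Opposite directions: 7.5%, 10.4% and 11.8% for the rank test on post scores at ρ = 0.5, 0.6 and 0.7, against 4.8%, 5.0% and 5.3% for the adjusted model. The rank test on change gives about 7 to 8%.

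These figures depend on the assumed slope. At a much steeper slope (1.5, about 21 to 22% lost), the rank test on post scores reaches 7.3% (ρ = 0.5) to 10.3% (ρ = 0.7) with dependence in one arm and 16.3% to 28.4% with opposite directions; the adjusted model stays at about 5%. Under those steep patterns the maximum likelihood estimate had bias near 0, against −0.12 SD (one arm) and −0.25 SD (opposite) for the raw completer difference.

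Steps 2 to 4 use baseline-adjusted regression on observed cases as a stand-in for the mixed model.

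**The case against.** Several counter-arguments have force.

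- **Transformation is the other option and is named first.** It keeps the mixed model, the covariates and the likelihood. A reader might infer that non-normality forces a switch to rank tests; the text only permits it. This stands, but nothing closes the other branch.
- **No test is named, and details may sit in an analysis plan not shown.** The cut-off for too much deviation and the choice of test could properly be left there, and their absence is not the point. What the article does state is an inspection of scores and a permitted replacement that does not fit its neighbouring commitments.
- **Scope.** The sentence follows one on descriptive and exploratory analyses, the later hypothesis paragraphs name mixed models without condition, and for the single-time-point FIT a rank test would lose nothing longitudinal. But the check covers all continuous scores, so applying the rule to the main outcomes is a fair reading.
- **Baseline adjustment is not promised.** The listed covariates do not include each outcome's own baseline; the plan tests change. The 12 to 13 point loss therefore measures the fallback against a stronger analysis than the one described. Against a change analysis it is 2 to 3 points.
- **Skew is when the rule fires.** In that setting rank tests can be as powerful or more so. The losses on normal data apply mainly where skewed scores hide adequate residuals.
- **Opposite-direction dropout is hypothetical.** The article plans continued measurement after treatment dropout ({18b}, {20c}), and its Discussion expects dropout to be low or comparable.

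**Conclusion.** The point holds in a limited form. The article judges normality on the wrong quantity and leaves open a remedy that cannot carry the covariates, the repeated measures or the maximum likelihood handling of missing data.

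A reader might infer that the fallback generally loses power or error control. The documents and calculations do not support that:

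- With normal residuals and correlation 0.5, the loss is about 12 to 13 points against a baseline-adjusted model and about 2 to 3 against an analysis of change.
- Under strong skew there may be no loss, or a gain.
- At moderate dependence of dropout on severity, type I error rises clearly (about 7 to 12%) only if the dependence runs in opposite directions by arm. That is an assumption, not something the article states. Steeper dependence would enlarge the problem and extend it to dependence in one arm.

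The more certain cost is to consistency: outcomes sent to rank tests would answer a different question, in completers only. This is worth correcting, but it does not undermine the trial.

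**What to change.** Replace the sentence on corrective steps in section {20a} with wording to this effect:

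*Normality will be assessed on the residuals and random effects of the fitted mixed model. Where these are clearly non-normal, the same longitudinal mixed model with its covariates remains the primary analysis, using a prespecified transformation, bootstrap or robust standard errors, or, for incident and frequency scores, a count or ordinal mixed model. Rank tests will be reported only as sensitivity analyses.*

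The remedy for each outcome should be named before the data are analysed by arm. The cost is one amended sentence and slightly more programming in SPSS for bootstrap, count or ordinal mixed models.

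### As described, the mixed models for the continuous primary scales appear to forgo adjustment for the outcome's own T0 value, which costs about 10 points of power at the plan's own inputs (about 2 to 17 over correlations of 0.7 to 0.3)

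*Protocol article*

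**What the plan says.** The statistical methods section ({20a}) gives the target of the continuous analyses: "to determine whether changes on continuous measures are different per treatment, we use linear mixed models". Table 4 lists three time points for TSCC, SIS, SIFS, SIM-PR and the Security scales, and four for CRIES. Table 3 measures the first group only at T0, T12/14 and T13, and CRIES also during treatment. The counts in Table 4 are reached only if T0 is one of the modelled occasions.

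The sample size section ({14}) powers the same kind of contrast, a "between 2 groups by within effect with at least two measurements (pre, end/follow-up" measurement, "with a power of 80% and a significance level of 5% (two-sided" level, with the correlation of 0.5 taken from the software default.

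Covariates are listed three times in {20a}, in nearly the same terms each time. One list reads: "We will control for child functioning, parental psychopathology, duration, severity, and intensity of interparental violence, and new IPV incidents". None of the lists names the T0 value of the outcome under analysis, and no sentence constrains the arms to a common mean at T0.

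**The concern.** If T0 is an outcome occasion with its own mean in each arm, the group-by-time contrast subtracts the whole baseline value instead of regressing on it. With equal variances and pre-post correlation rho, the variance of the contrast is proportional to 2(1 - rho), against 1 - rho² with baseline adjustment. The ratio of the second to the first is (1 + rho)/2, which is below 1 for every rho below 1.

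The listed covariates need not make up the difference. One that is constant over time and entered only as a main effect cancels out of a within-child change contrast.

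This matters because the sample size section says that study duration and the size of the eligible population limit recruitment. The plan expects 120 × 0.8 = 96 completers, or 32 per arm. A child's own T0 score is normally a strong predictor of later scores on the same scale, and it is already collected in every arm.

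**Working it through.** **Inputs** (sample size section {14}): f = 0.18; two-sided 5%; two groups; m = 2 measurements; rho = 0.5; sphericity; N = 64 per comparison.

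**1. Reproduce the plan's figure.** For the group-by-time test, the non-centrality is lambda = f² × N × m / (1 - rho) = 0.0324 × 64 × 2 / 0.5 = 8.29, with 1 and 62 degrees of freedom. Power is 80.9%. At N = 62 it is 79.6%, so 64 is the smallest even N that reaches 80%. The stated figure reproduces.

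**2. Express the effect in SD units.** In this 2 × 2 layout f = 0.18 equals a difference in change of 4 × 0.18 = 0.72 SD. The variance of a change score is 2(1 - 0.5) = 1 SD². Check: 0.72² × 64 / 4 / 1 = 8.29.

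**3. Adjust for baseline.** Same 0.72 SD effect, residual variance 1 - 0.5² = 0.75. Then lambda = 8.29 / 0.75 = 11.06 with 1 and 61 degrees of freedom, and power is 90.5%, a gain of 9.6 points. With adjustment, N = 48 gives 80.5%. A simulation of 20,000 trials with 32 per arm gave 80.6% and 89.6%.

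**4. Vary the assumptions** (0.72 SD and N = 64 unless stated).

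| Setting | Change contrast | Baseline-adjusted | Gain (points) |
|---|---|---|---|
| rho = 0.3 | 66.9% | 84.4% | 17.5 |
| rho = 0.4 | 73.5% | 87.1% | 13.6 |
| rho = 0.5 | 80.9% | 90.5% | 9.6 |
| rho = 0.6 | 88.7% | 94.3% | 5.6 |
| rho = 0.7 | 95.5% | 97.8% | 2.2 |
| rho = 0.5, all 80 per comparison complete | 88.9% | 95.6% | 6.8 |
| rho = 0.5, true effect 0.36 SD (assumption) | 29.4% | 37.3% | 7.9 |

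**5. Check the other reading.** Part of {20a} could be read as comparing levels at T12/T14. Without covariates, the variance factor is then 1 whatever rho is, so power is 80.9% throughout: against 90.5% adjusted at rho = 0.5, and against 97.8% at rho = 0.7. The listed covariates can recover part of that loss. If they explained 10% or 20% of the outcome variance (assumption), power for the level comparison would be 84.8% or 88.7%.

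**The case against.** The strongest reply is that the article never writes out the fixed effects. That T0 enters unconstrained is an inference from the stated target, the time-point counts and the powered contrast; a fuller analysis plan might say otherwise. This stands, and it is why the point is worded as what the models appear to do. It does not dispose of the point, because a covariate list given three times is a specification, and the most useful covariate is not on it.

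A second reply is that a group-by-time mixed model is valid in a randomised trial and is the contrast that was powered. That also stands. A reader might infer that the planned analysis is biased, or that 64 is too few on the plan's own terms. The documents support neither.

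Third, 10 points is not a general figure. The correlation is a default, not an estimate. The article quotes test-retest values of 0.82 for the SIFS and 0.75 for the Security Scale. Over a short interval these probably sit above the pre-post correlation, but at 0.75 the gain would be only about 1 point (98.0% to 99.0%). Children with partial data also contribute under maximum likelihood, which moves the gain from the 64-child figure towards the 80-child figure.

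Fourth, the covariate argument has limits. New incidents are measured repeatedly and do not cancel from a change contrast. For outcomes in the child-functioning, parental-psychopathology and violence domains, a listed covariate may be the same instrument at T0.

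**Conclusion.** The point holds as an efficiency loss in the analysis as described, and it is worth correcting. At the plan's own inputs, baseline adjustment is worth 9.6 points of power (80.9% to 90.5%), or 48 children in place of 64 for 80%. This rests on a 0.72 SD effect, equal variances, a correlation of 0.5 and 64 complete children. The gain grows at lower correlations and is small at 0.7 and above.

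It is clearest for CRIES, TSCC, SIS, SIFS, SIM-PR and the Security scales. A reader might carry the figure over to every primary outcome, but Table 4 assigns CAPS-CA to GEE as a categorical measure, and FIT has a single time point with no T0 value. Nor do the documents show that T0 is certainly left unconstrained; they only make that the natural reading.

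**What to change.** In {20a}, state that each continuous outcome with a T0 value is analysed with the post-baseline occasions as the response. The fixed effects are group, time, group-by-time, the outcome's T0 value and T0-by-time, in addition to the listed covariates. Report the adjusted group difference at each occasion as the treatment effect, and amend the time-point column of Table 4 to match.

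Keeping T0 in the response with a common mean across arms is an alternative only if T0 is completed before the family learns its arm. The concealment section ({16b}) has the measures start after the randomisation result has gone to the centre, so it does not secure this and should be clarified. A change-score analysis needs the same condition, so this is no reason to keep the present model.

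The cost is a short statement, a different model specification in SPSS, and one or two degrees of freedom per model. No new data are needed.
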